### **Data analyses**

Analyses will be undertaken on an intention to treat basis. The main experimental comparison is receipt of physical activity feedback (intervention) versus no feedback (control), with PAEE and DPA as the principal outcomes and self-reported physical activity, awareness and cognitions as secondary outcomes. Values at outcome, adjusted for baseline, will be compared between randomised groups. Gender, baseline physical activity and baseline awareness will be investigated as potential moderators of the intervention effect. In addition, we will conduct sensitivity analyses assuming a range of potential outcomes for non-completers informed by available baseline and interim data on this group. Non-completers will have multiple data imputed with a 'missing at random' assumption and with sensitivity analyses to represent optimistic and pessimistic scenarios for drop out. To assess mediating effects, a product-of-coefficient test will be used[49]. A secondary dose-response analysis will compare each feedback type ('Simple', 'Visual' or 'Contextualised') with the control condition and with each other.

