### ***Randomisation***

Once the Actiheart® monitor has been successfully downloaded and all relevant baseline data are available, participants are randomly allocated to either the control group or one of three feedback groups. Randomisation is carried out using a statistical minimisation programme (overseen by a statistician) on the basis of age ( $<45$ ,  $\geq 45$  years), gender (male/female), baseline physical activity level (PAL), an expression of the ratio of total energy requirements to basal metabolic rate over a 24-hour period ( $<1.63$ ,  $\geq 1.63$ ), body mass index ( $<27$ ,  $\geq 27$  kg/m^2) and glycosylated haemoglobin (HbA1c:  $<5.4$ ,  $\geq 5.4$  %), and is carried out independently of those undertaking baseline and follow-up measurements at the testing sites. Minimisation cut-offs were derived from an analysis of mean and median values in the first 1000 Fenland participants measured. Participants for whom sufficient baseline physical activity data is not available (less than 3 full days or 35 hours in total) are excluded from the study. Current data from the Fenland study suggest that this applies to fewer than 10% of participants. Since the FAB study is a trial of the impact of feedback of information, it is not possible to conceal group allocation from participants.

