### **Sample size**

Calculations were undertaken for a comparison between two equal-sized groups. Although the primary FAB analysis involves combining intervention groups and comparing them collectively against the control condition (intervention-control ratio = 3:1), secondary analyses compare each intervention group individually with the control group (intervention-control ratio = 1:1) and

each other, and will therefore require additional power. Calculations are therefore based on the secondary analyses.

Estimates are taken from the ProActive trial[50], which used a comparable population, age-group and primary outcome to those proposed here. Participants mean (SD) PAEE at baseline in this study was 0.116 (0.076)  $\text{kJ/kgFFM/min}$ . For a comparison between two groups, 100 participants per group completing follow-up would allow detection of a difference of 0.03  $\text{kJ/kgFFM/min}$  in physical activity energy expenditure (which equates to approximately 225 to 300 Kcal, or roughly 20 mins brisk walking per day) with 80% power at the 5% significance level. However, by adjusting for baseline values we obtain greater precision. The correlation between baseline and follow-up PAEE in ProActive was 0.58, meaning that 100 participants per group would allow detection of a difference of 0.025  $\text{kJ/kgFFM/min}$  (0.33 SD). Thus we aim to randomise a total of 500 participants, with the expectation that 400 (80%) would complete follow-up.

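### The main comparison adjusts for the baseline outcome value but does not carry age, gender, BMI and HbA1c over from the minimisation: a modest, nearly free gain in calibration and precision is left unused

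*Protocol*

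**What the plan says.** **Allocation.** Protocol, Randomisation: "Randomisation is carried out using a statistical minimisation programme (overseen by a statistician) on the basis of age" (cut at 45 years), gender, "baseline physical activity level (PAL), an expression of the ratio of total energy requirements to basal metabolic rate over a 24-hour period" (cut at 1.63), BMI (cut at 27 kg/m²) and HbA1c (cut at 5.4%). Allocation takes place only after the monitor has been downloaded and the relevant baseline data are in hand.

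**Analysis.** Protocol, Data analyses: "Values at outcome, adjusted for baseline, will be compared between randomised groups". The Abstract says the same. The main contrast is any feedback against none, "with PAEE and DPA as the principal outcomes". The Sample size section explains the adjustment through the correlation of 0.58 between baseline and follow-up PAEE, so "baseline" there is the baseline value of the outcome.

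**Other mention of the factors.** Data analyses: "Gender, baseline physical activity and baseline awareness will be investigated as potential moderators of the intervention effect". That concerns effect modification. It does not make gender or baseline activity a covariate of the main comparison.

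**The concern.** Minimisation makes the arms more alike on the chosen factors than chance would. Factors that also predict the outcome then contribute less to the true variance of the group difference. A model without them leaves their variance in the residual, so its standard error describes a less balanced trial than the one that was run. The interval is too wide, the nominal 5% test rejects less than 5% of the time under the null, and some precision is given away. All of this depends on the factors predicting follow-up activity after the baseline value has been taken into account.

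The factors that are clearly absent are age, gender, BMI and HbA1c. Baseline PAL comes from the same monitor recording as baseline PAEE and DPA, so the continuous baseline value should cover most, though not all, of what a PAL split at 1.63 carries.

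**Working it through.** **Inputs from the protocol (Sample size).** "Participants mean (SD) PAEE at baseline in this study was 0.116 (0.076" kJ/kgFFM/min), so SD = 0.076; r = 0.58; 100 completers per group; 80% power at 5%; target difference 0.03 unadjusted and 0.025 baseline-adjusted; 3:1 for the pooled comparison; 500 randomised, 400 completing.

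**Assumptions.** The test is two-sided (not stated). The partial R² of the omitted factors, given baseline, is not in the protocol and is varied from 0 to 0.20.

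**Step 1: reproduce the plan's figures.**
- Unadjusted detectable difference: 0.076 × (1.960 + 0.842) × √(2/100) = 0.0301. This agrees with the statement that "100 participants per group completing follow-up would allow detection of a difference of 0.03"; power at exactly 0.03 is 79.7%.
- Baseline-adjusted SD: s = 0.076 × √(1 − 0.58²) = 0.0619. Detectable difference: 0.0619 × 2.802 × √(2/100) = 0.0245. At 0.025 the power is 81.5%, and 0.025/0.076 = 0.33 SD, as stated.
- 400/0.80 = 500.
- Pooled 3:1 (300 v 100): SE = 0.0619 × √(1/100 + 1/300) = 0.00715. Power at 0.025 is 93.8%; the difference detectable with 80% power is 0.020.

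The plan's figures hold.

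**Step 2: effect of leaving the factors out.** Let SE be the standard error of the baseline-only model, based on s. With the factors balanced, the true standard error is SE × √(1 − R²), which is also what a model including them would report. Then:
- excess interval width = 1/√(1 − R²) − 1
- true size = 2 × [1 − Φ(1.960/√(1 − R²))]
- power, factors omitted = Φ[(0.025 − 1.960 × SE)/(SE × √(1 − R²))]
- power, factors included = Φ[0.025/(SE × √(1 − R²)) − 1.960]

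Example at R² = 0.10, 3:1: √0.90 = 0.9487 and the true SE is 0.00678. Size = 2 × [1 − Φ(2.066)] = 3.9%. Power omitted = Φ[(0.025 − 0.01401)/0.00678] = 94.7%. Power included = Φ(3.686 − 1.960) = 95.8%.

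| Partial R² | Interval too wide by | True size | 3:1 power, omitted v included | 1:1 power, omitted v included |
|---|---|---|---|---|
| 0 | 0% | 5.0% | 93.8 v 93.8% | 81.5 v 81.5% |
| 0.02 | 1.0% | 4.8% | 94.0 v 94.2% | 81.7 v 82.2% |
| 0.05 | 2.6% | 4.4% | 94.3 v 94.8% | 82.1 v 83.4% |
| 0.10 | 5.4% | 3.9% | 94.7 v 95.8% | 82.7 v 85.3% |
| 0.20 | 11.8% | 2.8% | 95.7 v 97.4% | 84.2 v 89.1% |

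The width and size columns depend on R² alone, so they apply to DPA as well. The power columns are for PAEE; the protocol gives no SD or correlation for DPA.

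**Step 3: simulation.** The formulas assume full balance among completers, whereas dropout undoes some of it. A simulation used 500 participants, four arms, five binary factors, an 80% biased coin, a correlation of 0.9 between baseline PAEE and PAL, 20% random loss and 1,500 runs per scenario. The coin and the 0.9 are assumptions. For R² of 0, 0.05, 0.10 and 0.20:
- Size of the baseline-only 3:1 test was 5.1%, 4.8%, 3.9% and 3.7%, against 5.1 to 5.3% with the factors included.
- The ratio of reported standard errors was 1.00, 1.02, 1.05 and 1.12.
- The 3:1 power gap at 0.025, for R² of 0.05, 0.10 and 0.20, was 1.1, 1.7 and 1.9 points, against 0.6, 1.1 and 1.7 from the formulas. Simulation error is about 0.6 points per estimate: √(0.05 × 0.95/1500).

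Direction and order of magnitude agree.

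**The case against.** **The text never says "only".** It is a one-sentence description that excludes no covariate, and a statistical analysis plan, which was not among the documents, could add some. This stands as a limit on the point. But the protocol does state an adjustment, states it twice and builds its sample size on it. That adjustment does not match the allocation scheme described a few sections earlier.

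**The error is on the safe side.** A reader might infer bias or an inflated false-positive rate. Neither follows: the baseline-adjusted comparison is unbiased, and its size is at or below 5%.

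**No planned power is lost.** A reader might infer an underpowered trial. The stated 80% already assumes adjustment for baseline alone and reproduces (81.5% at 1:1). What is forgone is measured against a better model.

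**All five factors and a large loss?** A reader might count PAL as unadjusted too, or expect several points of power at stake in the primary comparison. PAL is largely covered for PAEE and DPA. A larger gap in the 3:1 comparison appears if the true difference is near 0.020 (at R² = 0.10, 81.3% v 84.0%; at 0.20, 82.7% v 88.0%), but 0.020 is not a target the protocol sets.

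**The loss may be nil.** Correct: if the factors add nothing beyond baseline there is no effect, and the protocol gives no figure from which to judge.

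**Covariates cannot be added to every outcome without thought.** Also correct. Awareness is categorical, and in a logistic-type model added covariates change the effect being estimated.

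**Conclusion.** The point holds as a free improvement of modest size. The stated main comparison does not carry age, gender, BMI and HbA1c into the model although allocation was balanced on them.

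At an assumed partial R² of 0.02 to 0.10, intervals are about 1 to 5% too wide and true size is 4.8 to 3.9%. The power forgone at 0.025 is about 0.2 to 1.1 points for the pooled comparison and 0.5 to 2.6 points for the 1:1 comparisons on which the sample size rests. At R² = 0.10, the precision reported from 400 completers is what full adjustment would give from about 360 (400 × 0.90).

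The mismatch and its direction are secure. The size rests on the assumed R², a two-sided 5% test and near-balance of the factors among completers. The documents do not support any claim of bias, excess false positives or failure to reach the planned power.

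**What to change.** In Data analyses, state that the linear models for PAEE and DPA, for the pooled and the pairwise comparisons alike, include the baseline outcome value plus age, gender, BMI and HbA1c. For PAL, either add it or say that the continuous baseline value is taken to cover it. Put the same variables in the multiple-imputation model.

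For continuous secondary outcomes, use the same covariates and add PAL, because a baseline cognition score or self-reported activity does not stand in for it. For the categorical awareness outcome, state whether the reported effect is conditional on covariates or marginal.

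The cost is a few sentences and about five degrees of freedom out of 400. No new data are needed: minimisation requires each factor for everyone randomised. Naming the covariates in advance also removes any later choice guided by the results.

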### **Sample size**

Calculations were undertaken for a comparison between two equal-sized groups. Although the primary FAB analysis involves combining intervention groups and comparing them collectively against the control condition (intervention-control ratio = 3:1), secondary analyses compare each intervention group individually with the control group (intervention-control ratio = 1:1) and

each other, and will therefore require additional power. Calculations are therefore based on the secondary analyses.

Estimates are taken from the ProActive trial[50], which used a comparable population, age-group and primary outcome to those proposed here. Participants mean (SD) PAEE at baseline in this study was 0.116 (0.076)  $\text{kJ/kgFFM/min}$ . For a comparison between two groups, 100 participants per group completing follow-up would allow detection of a difference of 0.03  $\text{kJ/kgFFM/min}$  in physical activity energy expenditure (which equates to approximately 225 to 300 Kcal, or roughly 20 mins brisk walking per day) with 80% power at the 5% significance level. However, by adjusting for baseline values we obtain greater precision. The correlation between baseline and follow-up PAEE in ProActive was 0.58, meaning that 100 participants per group would allow detection of a difference of 0.025  $\text{kJ/kgFFM/min}$  (0.33 SD). Thus we aim to randomise a total of 500 participants, with the expectation that 400 (80%) would complete follow-up.

### **Data management**

Each participant is assigned a unique numeric identifier code at the beginning of the Fenland study so that they can be tracked without reference to personal information, and this will be continued to be used for the FAB study. As per usual Fenland procedures, all personal data is stored on an encrypted drive, and links to personal information are available only to the Fenland and FAB study coordination teams. Consent forms and questionnaire data are double-entered and stored in locked filing cabinets in secure Entacard-protected sites.

## **Ethics**

Full ethical approval for the FAB study was obtained from the Cambridge Local Research Ethics Committee on 4th June 2007 (reference number 07/Q0108/79). The study was registered under trial number ISRCTN92551397.

## **DISCUSSION**

There is increasing evidence that poor recognition of physical inactivity may be an important barrier to healthy behaviour change. Compelling observational data suggest that in terms of physical activity attitudes and intentions, people who incorrectly believe that their physical activity is adequate are comparable to those who achieve the recommended guidelines[5, 9, 51] and thus resemble a group that public health interventions may not be able to reach. The FAB trial is designed to explore the effect of feedback on physical activity awareness, cognitions and behaviour in a population-based sample. In addition to estimating efficacy, it will provide information on possible psychological mechanisms of behaviour change. FAB has the potential to establish the extent to which increasing the accuracy of peoples' self-perceptions of physical activity might facilitate healthy behaviour change. However, it will also allow for the assessment of the risk for false-reassurance.

Our trial has been designed to address the limitations of previous work in the area of physical activity awareness and feedback. The use of a combined HR and movement sensor to assess physical activity overcomes the limitations associated with self-reported physical activity behaviour or intentions and is more accurate than either heart-rate monitoring or accelerometry alone [29]. By drawing on relevant theory and evidence, we have chosen covariates with evidence of predictive ability for measurement at baseline and follow-up. These are expected to facilitate identification of possible moderators and mediators of behaviour change.

FAB is the first randomised trial of the effects of measurement and feedback on physical activity awareness, cognitions and behaviour using an objective measure of behaviour change and a population-based sample. Findings will be relevant to future studies that try to explain and change health behaviours in general and those on misperceptions about health behaviours in particular. Overall, it is expected that this will help inform the design of future preventive programmes promoting physical activity.

### **COMPETING INTERESTS**

The authors declare that they have no competing interests.

49. Krull JL, MacKinnon DP: **Multilevel Modeling of Individual and Group Level Mediated Effects.** *Multivariate Behavioral Research* 2001, **36**(2):249 - 277.
50. Kinmonth A-L, Wareham NJ, Hardeman W, Sutton S, Prevost AT, Fanshawe T, Williams KM, Ekelund U, Spiegelhalter D, Griffin SJ: **Efficacy of a theory-based behavioural intervention to increase physical activity in an at-risk group in primary care (ProActive UK): a randomised trial.** *The Lancet* 2008, **371**(9606):41-48.
51. Smeets T: **Towards a healthy lifestyle: the development and evaluation of a computered tailored lifestyle intervention. PhD thesis.** Maastricht University, Faculty of Health Sciences; 2006.

**Table 1.** Reference values for physical activity levels (PAL) as published by FAO/WHO/UNU [30]

| PAL Value  | Description                                                           |
|-------------------|------------------------------------------------------------------------------|
| Less than 1.2     | Bed rested: Most likely when in care of others                               |
| 1.2 to 1.55       | Low activity level: Sedentary lifestyle.                                     |
| 1.55 to 1.71      | Medium activity level: Occasionally active. Typical office work.             |
| 1.71 to 1.95      | High activity level: Some manual work and/ or regular exercise               |
| Greater than 1.95 | Very high activity level: A fair amount of manual work or exercise training. |

**Table 2:** FAB trial measurements and their timing

|                                                                                  | Baseline
visit | Mailout 1 (~2
wks post-
baseline) | Mailout 2 (~5
wks post-
Mailout 1) |
|----------------------------------------------------------------------------------|-------------------|-----------------------------------------|------------------------------------------|
| Main outcome                                                              |                   |                                         |                                          |
| 1. PA – 6-day heart rate and movement monitoring
(Actiheart®)                 | ✓                 |                                         | ✓                                        |
| Other outcomes                                                            |                   |                                         |                                          |
| 2. PA awareness                                                                  | ✓                 |                                         | ✓                                        |
| 3. Fenland measures (anthropometry, body
composition, fitness)                | ✓                 |                                         |                                          |
| 4. Self-reported PA                                                              | ✓                 |                                         | ✓                                        |
| 5. Self-rated PA: a                                                   |                   |                                         |                                          |
| i. Absolute (WHO categories)                                                     | ✓                 | ✓                                       | ✓                                        |
| ii. Relative (peer comparison)                                                   | ✓                 | ✓                                       | ✓                                        |
| iii. According to guidelines (CMO)                                               | ✓                 | ✓                                       | ✓                                        |
| 6. Confidence in self-rated PA a                                      | ✓                 | ✓                                       | ✓                                        |
| 7. PA Subjective norms a                                              | ✓                 | ✓                                       | ✓                                        |
| 8. Worry/ concern about PA a                                          | ✓                 | ✓                                       | ✓                                        |
| 9. Perceived behavioural control/self efficacy a                      | ✓                 | ✓                                       | ✓                                        |
| 10. Behavioural beliefs a                                             | ✓                 | ✓                                       | ✓                                        |
| 11. Perceived importance of physical activity for
health a         | ✓                 | ✓                                       | ✓                                        |
| 12. Intention to change PA a                                          | ✓                 | ✓                                       |                                          |
| 13. Time orientation (concern about current/future
consequences) a | ✓                 |                                         |                                          |

PA: Physical activity; WHO: World Health Organisation; CMO: Chief Medical Officer

a: included in FAB questionnaire

**Table 3:** Description of the three types of self-rated physical activity measured in the FAB study.

| Category    | Reference standard                            | Question used (answer categories)                                                                                                                                                                                                                                        |
|-------------|-----------------------------------------------|--------------------------------------------------------------------------------------------------------------------------------------------------------------------------------------------------------------------------------------------------------------------------|
| Absolute    | PAL categories defined by WHO categories [30] | On average, which category do you believe best describes your general level of physical activity? (Bed-rested/ Low/ Medium/ High/ Very High).                                                                                                                            |
| Relative    | Peer comparison                               | In your opinion, compared to other people of your age and sex, how physically active are you? (Much less/ A little less/ About the same/ A little more/ Much more).                                                                                                      |
| Recommended | CMO guidelines [40]                           | According to national recommendations people should be active at a moderate intensity (e.g. brisk walking) for at least 30 minutes per day at least 5 days a week. Please indicate whether you think you achieved this level of activity over the last month. (Yes/ No). |

Figure 1

[figure not shown]

[figure not shown]

**Figure 3.** Classification of participants into awareness categories

|                                        |          | Self-rated physical activity |                         |
|----------------------------------------|----------|------------------------------|-------------------------|
|                                        |          | Active                       | Inactive                |
| Objectively measured physical activity | Active   | Realistic Active (RA)        | Underestimator (UE)     |
|                                        | Inactive | Overestimator (OE)           | Realistic Inactive (RI) |

Figure 3
